#### Primary outcome analysis

The impact of the PI intervention on the resumption of CPAP treatment will be studied by comparing the resumption of CPAP in the two arms, using a χ^2^ test. To take into account a possible centre effect, a second analysis will be carried out using a conditional logistic regression stratified by the centre; the intervention or control arm will be considered as the dependent variable.

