#### Description of the intervention

Trained peers will meet patients randomised into the intervention group by videoconference. Each PI representative will be allocated 5–8 patients. They will conduct three face-to-face motivational sessions, each of 45–60 min duration, over a 6-month period based on the principle of motivational enhancement and cognitive-behavioural therapies.^11 13^ The content of the first session is designed to identify and understand the underlying reasons for stopping CPAP treatment and to identify difficulties encountered by the patient (advantages and disadvantages of CPAP treatment). The aim of the second session will be for the patient to define his/her objectives and priorities. During the last session, will be discussed to strengthen the motivation to change and how to plan for it. The peers will receive €100 per patient for the three interviews.

In the control group, patients will be informed, at inclusion, that they can have a visit with a physician investigator at any time to resume treatment if they wish, as is usual practice. At the end of the 6-month follow-up period, all patients in both groups will have a consultation with their physician who will suggest they resume CPAP treatment. This visit may take place earlier if the patient wishes to resume CPAP treatment before the end of the follow-up period. We planned to start inclusions by November 2021 and end the study by December 2023.

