### Statistical analysis

#### Sample size

We hypothesise that 20% of patients allocated to the intervention group will reuse CPAP 6 months as compared with 6% of patients in the control group. A two group χ² test with a 5% two-sided significance level will have 80% power to detect such difference between the two groups when the sample size in each group is 90 (nQuery V.8, Statistical Solutions, Cork, Ireland). In order to take into account a possible drop-outs and to comply with the intention-to-treat principle, we will inflate the sample size by a factor of 15%.^32^ We, thus, plan to include 104 patients per group (ie, 208 patients in total). Fifteen patient peers will be involved.

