Despite these strengths, the study has two main inherent limitations. First, the results are likely to be biased by the fact that patients who accept to participate may be more likely to resume CPAP therapy than those who decline participation. The results may therefore not be generalisable to all patients who have stopped using their CPAP as prescribed. Second, the effectiveness of the intervention may also depend on the capacity of the peer-participant to deliver it. The training is quite short (three half-days) and some of the peers recruited may be more skilled than others in providing such intervention. However, in this study, the peers will be additionally supported throughout the study by the DUP.

In summary, the results of this study will determine the effectiveness of a PI intervention to motivate patients who have stopped using their CPAP as prescribed to resume its use on compliance with CPAP therapy. The results will also provide information regarding the factors relating to resumption of CPAP, providing a starting point for further studies to determine the most appropriate methods to improve compliance in those patients who benefit less from PI interventions.

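### The primary chi-square, the centre-stratified models and the sample size treat intervention patients as independent, although they are nested in 15 peers who are expected to differ in skill

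*Protocol article*

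**What the plan says.** Under Description of the intervention, the protocol has trained peers hold three motivational sessions with every intervention patient: "Each PI representative will be allocated 5–8 patients". Under Sample size it adds "Fifteen patient peers will be involved". Control patients have no peer.

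Under Primary outcome analysis, the effect "will be studied by comparing the resumption of CPAP in the two arms"; the sentence goes on to name a chi-square test. A second analysis uses conditional logistic regression stratified by centre. Under Secondary outcomes analyses, the adherence models also carry centre only.

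The sample size assumes that "20% of patients allocated to the intervention group will reuse CPAP 6 months", against "6% of patients in the control group". It states: "A two group χ² test with a 5% two-sided significance level will have 80% power" "when the sample size in each group is 90", with the gap between these two phrases stating only that this is the difference to be detected. The 90 is then raised by 15% for drop-outs, to 104 per group.

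The Discussion gives as one of the study's two main limitations that "the effectiveness of the intervention may also depend on the capacity of the peer-participant to deliver it". It adds that the training is short and that peers may not be equally skilled. The strengths-and-limitations box names homogeneous peer skills as a challenge.

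**The concern.** This is a partially nested design: clusters exist in one arm only. If peers differ in how well they persuade patients, two patients of the same peer have more similar outcomes than two patients of different peers. The variance of the intervention-arm proportion is then larger than the binomial variance that the chi-square uses.

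Two things are at stake. One is the precision claimed for the primary result. The Discussion looks to an evidence base for peer involvement in general, which is a conclusion about peers beyond the 15 in the trial. The other is the stated 80% power, which is calculated as if patients were independent.

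Stratifying by centre does not settle this, because it addresses differences between centres, not between peers. Nor is this detail left to a separate analysis plan: the test, the second model and the sample size are all stated, and each omits peer.

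**Working it through.** **Inputs from the protocol.** p1 = 0.20, p2 = 0.06, two-sided 5%, 90 per group before inflation and 104 after, 15 peers, 5 to 8 patients per peer.

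**Assumed.** ICC = 0.02, 0.05 or 0.10, since the protocol gives none. To judge this range: the standard deviation of true resumption rates between peers is √(ICC × p1(1 − p1)) = √(ICC × 0.16). That is 5.7, 8.9 and 12.6 percentage points around a mean of 20%.

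**Step 1: reproduce the plan.** The pooled-variance two-proportion formula without continuity correction gives n = 90 per group, with power 80.3%. 90 × 1.15 = 103.5, rounded up to 104, where power is 85.7%. The plan's figures are reproduced exactly, with independent patients.

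**Step 2: design effect, intervention arm only.** m = 104/15 = 6.9 patients per peer with all analysed. With 15% lost, n = 104 × 0.85 ≈ 88 and m = 88/15 = 5.9. DE = 1 + (m − 1) × ICC.

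**Step 3: type I error of the plain chi-square** when the average effect is zero but peers vary: 2 × [1 − Φ(1.96/√((1 + DE)/2))].

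**Step 4: power of an analysis with the correct variance.** With p̄ = 0.13:
- SE0 = √((1 + DE) × 0.13 × 0.87/n)
- SE1 = √((DE × 0.16 + 0.0564)/n)
- power = Φ((0.14 − 1.96 × SE0)/SE1)

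Example with n = 104 and ICC 0.05: DE = 1.297, SE0 = 0.0500, SE1 = 0.0504, so power = Φ(0.835) = 79.8%.

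| Assumed ICC | DE (104 / 88) | Type I error of chi-square (104 / 88) | Power allowing for peer (104 / 88) |
|---|---|---|---|
| 0 | 1.00 / 1.00 | 5.0% / 5.0% | 85.7% / 79.4% |
| 0.02 | 1.12 / 1.10 | 5.7% / 5.6% | 83% / 77% |
| 0.05 | 1.30 / 1.24 | 6.7% / 6.4% | 80% / 74% |
| 0.10 | 1.59 / 1.49 | 8.5% / 7.9% | 74% / 69% |

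**Step 5: simulation of the plain chi-square** (beta-binomial, 15 peers, independent controls, 200,000 runs).
- Type I error at a common rate of 6%, ICC 0.02 / 0.05 / 0.10: 5.5% / 6.4% / 8.1% with 104 per arm and 4.9% / 5.6% / 7.1% with 88. At common rates of 13% and 20% it reaches 5.8% / 6.9% / 8.8% with 104.
- Rejection rate at 20% against 6%, same ICCs: 87% / 86% / 84% with 104 and 81% / 80% / 79% with 88.

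**Step 6: small-sample correction.** The intervention-arm variance rests on 15 peers, so 14 degrees of freedom. A Satterthwaite combination with the control arm gives about 22 to 23 degrees of freedom at ICC 0.05 and a critical value of about 2.07 instead of 1.96. Power at ICC 0.05 is then about 76% with 104 and 70% with 88.

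**The case against.** Four points can be made for the plan.

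*Patients are randomised individually.* If peers have no effect at all and patients are assigned to them unselectively, there is no clustering under the null and the chi-square keeps its level. This stands. A reader might infer that the trial's 5% error rate is simply broken, but the protocol does not support that. Inflation requires peers who differ while their average effect is zero, so that some do better than no peer and some worse. The understated uncertainty for conclusions beyond these 15 peers does not need that condition. It arises whenever peers differ.

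*The ICC is unknown.* This also stands. At 0.02 or below the effect is negligible, and it becomes material from about 0.05. Confidence is high that the clustering exists, but not about its size.

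*The planned test keeps its power.* A reader might infer that the chi-square will miss its 80%. Simulation does not bear this out: it still rejects about 79-81% of the time with 88 per arm and 84-87% with 104. The loss belongs to an analysis that allows for peer. At 88 per arm, independence alone already gives only 79.4%, so not all of the gap to 80% is due to clustering.

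*The 15% inflation is a buffer.* In part. Resumption is defined by prescription and set-up of a new device by the homecare provider, so most of the 104 may well be analysable. Power then stays near 80% up to ICC 0.05 by the normal approximation. But the inflation was assigned to drop-out and cannot fully serve both purposes.

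**Conclusion.** The point holds and should be fixed; it does not invalidate the trial. Intervention patients are nested in peers whom the protocol expects to differ, and the stated test, models and sample size leave this out.

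The direction matters: the nominal 5% understates the true error rate if peers vary around a zero average effect, and the 80% overstates the power of an analysis that allows for peer. On an assumed ICC of 0.02 / 0.05 / 0.10, type I error is about 5-6% / 6-7% / 7-9%. Cluster-valid power is about 83 / 80 / 74% with 104 per arm and 77 / 74 / 69% with 88, by normal approximation. With a small-sample correction it falls to about 76% and 70% at ICC 0.05.

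These figures rest on the assumed ICC range, near-equal numbers per peer and the plan's own 20% and 6%. The estimated difference between arms is unaffected; its stated precision is what changes.

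**What to change.** Before outcome data are seen, pre-specify an analysis of resumption that allows for peer in the intervention arm only, as the primary analysis or at least alongside the chi-square. There are two options:

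- Peer-clustered robust variance with a small-sample correction for 15 clusters, each control being its own cluster.
- A partially nested model with a peer random effect in the intervention arm. This is acceptable only if it proves stable: about 27 events are expected (104 × 0.20 ≈ 21 plus 104 × 0.06 ≈ 6), and centre terms must be carried as well.

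Use the same structure for the adherence outcomes. Record the treating peer for each intervention patient. Peers are allocated patients and paid per patient, so the link is probably known, but the protocol does not say that it is captured in the study database. Report the peer ICC with the results. Restate power over a range of ICC with the same small-sample correction that the analysis will use.

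No patients need be added, provided the lower power is stated openly. The cost is statistical wording, one recorded variable, a slightly wider interval and a less favourable stated power.

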## Methods and analysis

### Study design

This is a prospective, multicentre, randomised controlled trial that will be coconducted by health professionals, a CPAP home provider and patients as experts or peers or participants. After signing a consent form, patients’ participants will be randomised 1.1 to the intervention group with peers or the control group. Nota bene: the peers involved in the conduct of the study will sign a confidentiality agreement of non-divulgation of the information exchanged with the participants.

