#### Randomisation

After consent, randomisation will be performed by a centralised computer software for each investigating centre. It will be stratified on the centre.

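### Randomisation is stratified by centre, but the lead primary test is an unstratified chi-square; making a centre-stratified analysis primary would cost nothing

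*Protocol article*

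**What the plan says.** On allocation, the Randomisation section of the protocol article states: "It will be stratified on the centre". Allocation is 1:1 (Study design).

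The Primary outcome analysis section first compares resumption between arms with a chi-square test that has no centre term. It then continues: "To take into account a possible centre effect, a second analysis will be carried out using a conditional logistic regression stratified by the centre". The same sentence names the study arm as the dependent variable of that regression.

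The Sample size section is built on the same unstratified test: "A two group χ² test with a 5% two-sided significance level will have 80% power to detect such difference between the two groups". The assumed rates are 20% with the intervention and 6% in control.

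The Secondary outcomes analyses section treats centre differently. Mean compliance is analysed in a mixed model with centre as a random factor. Resumption with adequate adherence is analysed by conditional logistic regression stratified by centre, and so are the factors associated with resumption. In each case that is the main stated method.

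**The concern.** A factor used to stratify randomisation should normally appear in the main analysis. Stratified allocation makes the arms more alike in centre mix than simple randomisation would. The plain chi-square takes no credit for this: its variance still contains the between-centre component, although that component no longer contributes to the difference between arms. Its standard error is therefore somewhat too large whenever resumption rates differ between centres.

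At stake is a little power, and consistency within the plan. The lead primary test is the only between-arm efficacy comparison that leaves centre out, while the adherence comparisons all include it. The tests are named in the article, so this is a stated choice and not a detail deferred to another document.

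**Working it through.** **1. The plan's own figure.** Inputs from Sample size: 20% versus 6%, two-sided 5%, 80% power, unstratified chi-square. The mean rate is 0.13 and the difference 0.14.

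n = [1.960·√(2·0.13·0.87) + 0.8416·√(0.20·0.80 + 0.06·0.94)]² / 0.14²
= (0.932 + 0.392)² / 0.0196 = 1.752 / 0.0196 = 89.4, rounded up to 90.

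The stated 90 per group is reproduced (power at 90: 80.3%). Then 90 × 1.15 = 103.5, rounded up to 104 per group, or 208 in total. The planned size follows from its inputs.

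**2. A worked example of the conservatism.** The documents give neither the number of centres nor centre-specific rates. Assume three equal centres with resumption rates of 5%, 10% and 20% in both arms.

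- Mean rate: 0.35 / 3 = 0.1167.
- Total variance: 0.1167 × 0.8833 = 0.1031.
- Between-centre variance: (0.0667² + 0.0167² + 0.0833²) / 3 = 0.0039.
- Share of total: 0.0039 / 0.1031 = 3.8%.
- Standard error too large by a factor 1/√0.962 = 1.019, about 2%.
- True type I error: 2·[1 − Φ(1.96 × 1.019)] = 0.046.

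Simulating the same example (200,000 trials, 104 per group, 1:1 within centre) gives a type I error of 4.7% for the chi-square and about 5.0% for the Mantel-Haenszel test. With the same spread on the log-odds scale shifted to 6% versus 20% overall, power is about 88% for both, the stratified test being 0.4 points higher.

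**3. A wider range of assumptions.** Simulations of 40,000 trials per scenario used 3, 5 or 8 equal-sized centres, exact 1:1 allocation within centre, and a common rate of 6% or 13% under the null. The stratified test is Mantel-Haenszel, which is the score test of centre-stratified conditional logistic regression. Ranges run over the three numbers of centres.

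| SD of centre log-odds | Chi-square type I error, rate 6% | Chi-square type I error, rate 13% | Power at 104, chi-square | Power at 104, stratified | Gain (points) |
|---|---|---|---|---|---|
| 0 | 4.7–4.9% | 5.1–5.3% | 87.5–87.8% | 87.3–87.7% | −0.2 to −0.1 |
| 0.5 | 4.3–4.6% | 4.6–4.9% | 87.9–88.2% | 88.1–88.4% | 0.2 |
| 1.0 | 4.3% | 4.0–4.2% | 88.4–89.0% | 89.8–90.4% | 1.2–1.5 |
| 1.5 | 3.5–4.1% | 3.1–3.5% | 89.3–90.1% | 91.7–93.0% | 2.4–2.9 |

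The stratified test's type I error stays between 4.5% and 5.3% throughout. Simulated power at 104 with no centre effect (about 88%) is a little above the large-sample formula (85.7%); the contrast between the two tests is what matters here. If only 90 per group were analysed, the gain would be 0.5 points at SD 0.5, 2.0–2.2 at SD 1.0 and 3.5–4.2 at SD 1.5.

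**4. The direction of the regression.** With only arm and resumption in the model, both binary, the centre-stratified odds ratio and its test are the same whichever variable is called dependent. The p-value of the second analysis is therefore unaffected. The model is nevertheless described backwards, and that would matter once covariates were added.

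**The case against.** The strongest reply is that centre is already handled. The stratified analysis is pre-specified, so the proposal only exchanges the roles of two planned analyses. The chi-square errs on the cautious side and carries no false-positive risk from omitting centre. With little centre variation nothing is lost, and the extent of that variation is unknown. All of this stands, and it limits the point to an improvement.

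A reader might also infer that the two primary analyses are unranked, so that the trial's conclusion is open to choice between two p-values. The documents do not support that. The chi-square is named first and without qualification, the regression is introduced as second and for a limited purpose, and the sample size is computed for the chi-square. All three point to the chi-square as the lead test. An explicit rule for discordant results is the kind of detail that an article may leave to the full plan. Discordance would also be rare: in the simulated 5/10/20% example the two tests fell on different sides of 5% in about 0.2% of trials under the null and 0.4% under the alternative, almost always with the stratified test the significant one. Wald or likelihood-ratio tests from the fitted model might disagree somewhat more often.

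Two other inferences fail on the calculations: that omitting centre inflates the type I error (it lowers it when centres differ), and that the sample size must change (it need not).

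**Conclusion.** The point holds as a modest one. The lead primary test ignores the factor on which randomisation was stratified, while the between-arm adherence analyses account for it. The chi-square is valid but mildly conservative when centres differ. In the 5/10/20% example the true type I error is about 4.6–4.7%. At 104 per group the power loss is under 1 point with modest centre variation, roughly 1.2–1.5 points at a log-odds SD of 1.0, and about 2–3 points only at an SD of 1.5. With no centre variation there is no loss.

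These sizes rest on assumed numbers of centres, equal centre sizes and assumed spread. The reading of the text does not depend on them, and neither does the direction of the effect when centres differ.

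**What to change.** Name one centre-stratified analysis as primary. Either of these would serve:

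- a Cochran-Mantel-Haenszel test stratified by centre, reported with a stratified risk difference and its confidence interval; or
- centre-stratified logistic regression with resumption of CPAP as the outcome and study arm as the explanatory variable, which also corrects the clause that makes arm the dependent variable.

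Keep the plain chi-square and label it a sensitivity analysis. The target of 104 per group (208 in total) can stay: in the scenarios tried, the stratified test has at least the same power once centres differ, and gives up at most 0.2 points when they do not. The cost is a change of wording, with no extra data or patients.

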#### Secondary outcomes analyses

Mean CPAP compliance 1 month after resumption of CPAP will be analysed using a mixed linear model (fixed factor: randomisation arm (intervention vs control), random factor: centre). Comparison of the probability of resuming CPAP with an average compliance of at least 4 hours/night, 70% of nights between the intervention and control groups will be analysed using a conditional logistic regression, stratified by centre. All analyses will be performed as intention-to-treat and then a sensitivity analysis will also be performed per protocol (patients who have not resumed treatment will be considered to have zero adherence).

The association between resumption of CPAP and the sociodemographic parameters, clinical data and the scores of the three questionnaires will be studied by conditional logistic regression models stratified by centre, and adjusted by arm (intervention vs control).

In the intervention arm, descriptive statistics will be presented on the satisfaction as well as on the number of interviews carried out and their average duration.

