#### Secondary research outcomes

Average adherence to CPAP will be measured from data recorded by the built-in software of the CPAP devices (via tele monitoring or retrieved by a home technician) for 1 month after the final consultation.The relationship between the variables below and a positive response to the peers intervention (defined by a restart of CPAP treatment) will be analysed: age, gender, body mass index, marital status and number of young children (<10 years) education level, socioprofessional status, fragility and social precariousness (using the EPICES score), smoking and alcohol use, comorbidities (using Charlson score), history of OSAS (date of diagnosis of OSAS, baseline AHI), observance to treatments (Girerd score), date and reason for stopping CPAP and EDS score (using the Epworth Sleepiness Scale). To determine patient profiles, their representations of OSAS, their experiences with CPAP and their knowledge and confidence to manage their health, three questionnaires will be completed at inclusion (M0) and at the 6-month follow-up (M6): the Functional Outcomes of Sleep Questionnaire a disease-specific quality of life questionnaire,^28^ the patient activation measure a measure that assesses patient knowledge, skill and confidence for self-management^29^ and the Self-Efficacy Measure for Sleep Apnoea^30 31^ a tool with strong psychometric properties that identifies patient perceptions that may indicate those most likely not to adhere to treatment.The satisfaction of participating patients with the PI intervention and the satisfaction of PI representatives will be measured on a 4-point Likert scale: very dissatisfied, dissatisfied, satisfied, very satisfied.The feasibility and the execution of the three interviews will be assessed by the number of interviews carried out in their entirety and the average duration of each interview (in minutes).

All information will be collected in secure electronic medical records in accordance with the requirements of general data protection regulation.

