### Statistical analysis plan

#### Descriptive analyses

Continuous variables will be expressed as medians (25th/75th percentiles) or means (SD) depending on normality which will be assessed with the Shapiro-Wilk test. Categorical variables will be reported as absolute numbers and percentages for both groups. Baseline comparisons between groups will be made using a Student’s t-test or Mann-Whitney U test, depending on the distribution. For discrete variables, a χ^2^ test will be used. If significant differences are observed between arms, analysis of variance and multivariable regression will be performed. In the case of missing data, an imputation strategy will be applied according to the percentage of missing values. Data management and statistical analyses will be performed using SAS, V.9.4, SAS Institute.

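### The zero-adherence rule for non-resumers is attached to the per-protocol analysis, leaving the intention-to-treat comparison of mean CPAP use without a value for patients who never resume

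*Protocol article*

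**What the plan says.** The protocol article's section on secondary outcomes analyses describes two adherence comparisons.

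- **Mean use:** "Mean CPAP compliance 1 month after resumption of CPAP will be analysed using a mixed linear model", with randomisation arm as fixed factor and centre as random factor.
- **Binary adherence:** "Comparison of the probability of resuming CPAP with an average compliance of at least 4 hours/night, 70% of nights", by conditional logistic regression stratified by centre.

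One sentence then covers the analysis sets. It opens with "All analyses will be performed as intention-to-treat" and continues with "a sensitivity analysis will also be performed per protocol (patients who have not resumed treatment will be considered to have zero adherence". The zero rule is thus in a parenthesis directly after the words per protocol.

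Two other places bear on the point. The section on secondary research outcomes takes average adherence from the device's built-in software, "for 1 month after the final consultation", which is a different time anchor. The section on descriptive analyses says of missing data that "an imputation strategy will be applied according to the percentage of missing values".

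**The concern.** Setting non-resumers to zero is what an intention-to-treat comparison of mean use needs. Under the eligibility rules, patients enter the trial after returning their device. Someone who never resumes has no machine from the provider, and zero hours is the natural value. Failure to resume is an outcome and not a deviation from protocol, so the per-protocol clause is an odd place for the rule.

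Followed to the letter, the mixed model has no value for non-resumers in the main analysis, and they drop out. Those who remain are selected on resumption, which is the primary outcome and is expected to differ between arms. That breaks the randomised contrast, although the first secondary aim is to compare adherence between the randomised groups. The general imputation sentence adds a further risk: if a non-resumer's use were treated as missing, positive hours could be imputed for a patient with no device.

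**Working it through.** **Inputs from the protocol article.** The sample size section assumes that "20% of patients allocated to the intervention group will reuse CPAP 6 months as compared with 6% of patients in the control group". It gives 90 per group, inflated by 15% to 104 per group (208 in total), and states: "A two group χ² test with a 5% two-sided significance level will have 80% power". It gives no expected hours of use and no power for adherence.

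**Reproducing the plan's figure.** With the pooled-variance formula, no continuity correction and a mean proportion of 0.13:

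n = [1.960 × √(2 × 0.13 × 0.87) + 0.842 × √(0.20 × 0.80 + 0.06 × 0.94)]² / 0.14² = 89.4, so 90 per group (power 0.803). Then 90 × 1.15 = 103.5, so 104. Both stated figures reproduce, and the rates can be used as they stand.

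**Patients left in a resumers-only mean.**

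- Intervention: 104 × 0.20 = 20.8, about 21.
- Control: 104 × 0.06 = 6.24, about 6.
- Together about 27 of 208, so about 181 randomised patients contribute nothing.
- With 90 per group the counts are 18 and 5.4.

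**Direction of the two contrasts.** Assumptions not in the document: the 6% who would resume unaided average 4 h/night in either arm, and the extra 14% in the intervention arm average x h/night.

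- Resumers only: (0.06 × 4 + 0.14x)/0.20 - 4 = 0.7(x - 4).
- All randomised, zeros for non-resumers: (0.06 × 4 + 0.14x) - 0.06 × 4 = 0.14x.

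| x (h/night) | Resumers only (h) | All randomised (h) |
|---|---|---|
| 2 | -1.40 | +0.28 |
| 2.5 | -1.05 | +0.35 |
| 3 | -0.70 | +0.42 |
| 4 | 0 | +0.56 |
| 5 | +0.70 | +0.70 |

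The signs are opposite for every x between 0 and 4, and agree above 4. Setting the unaided resumers at 5 h/night gives the same pattern: for x from 2 to 5 the resumers-only difference runs from -2.1 to 0 h, and the all-randomised difference from +0.28 to +0.70 h.

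**Precision.** The standard error of the resumers-only contrast is SD × √(1/20.8 + 1/6.24) = 0.456 × SD. For an assumed SD of 1.5, 2 or 2.5 h it is 0.68, 0.91 or 1.14 h, and the 95% confidence half-width is 1.34, 1.79 or 2.24 h.

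For the all-randomised contrast with x = 4, the variance in each arm is p(SD² + 4²) - (4p)². With SD 2 h this is 3.36 for intervention and 1.14 for control, so the standard error is √((3.36 + 1.14)/104) = 0.21 h against a difference of 0.56 h. Over the same SD range, power is about 81% down to 72%. It is lower if the extra resumers use CPAP less.

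**The case against.** The strongest reply is that the plan nowhere restricts the mean comparison to resumers. The sentence opens by declaring every analysis intention-to-treat, and its closing parenthesis can be read as covering both analyses. On that reading the zero rule already applies where it is needed. This stands as far as it goes. A reader might infer that the plan has decided to compare resumers with resumers, but the text does not say so. It is the literal consequence of where the rule is placed, in a sentence that is ambiguous or at odds with itself.

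A reader might also extend the point to all adherence analyses. That does not hold. The binary comparison concerns resuming with adequate use, so a non-resumer counts as a failure by definition and every randomised patient has a value.

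A third tempting reading is that the intervention would appear harmful. The documents give no hours of use and no evidence that the extra resumers would use CPAP less, and the reversal disappears if they use it as much as unaided resumers. Even at x = 2.5, the -1.05 h is about one standard error for an SD of 2 to 2.5 h, so a significant result in the wrong direction would be uncommon.

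The time anchor in the outcomes section is not conditional on resumption, which weakens the claim that the endpoint exists only for resumers. But that section also takes adherence from device recordings and gives no value for patients without a device. The two anchors therefore need reconciling, and neither settles the question.

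Finally, a condensed article may leave detail to a fuller analysis plan. That would excuse silence. Here a rule is stated, and it is attached to the wrong analysis.

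**Conclusion.** The point holds for one analysis, the comparison of mean CPAP use. Its main analysis has no stated value for non-resumers, and the rule that would supply one is tied to the per-protocol analysis. Taken literally, the comparison rests on about 21 against 6 patients selected on the primary outcome.

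The patient counts follow from the plan's own rates. The possible reversal of sign rests on assumed hours and requires the extra resumers to use CPAP less than unaided resumers. Selection after randomisation is a problem whichever way it goes. So is an ambiguity that lets the analyst choose, after seeing the data, between two analyses that may disagree.

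The primary chi-square test, the sample size and the binary adherence comparison are not affected. This should be fixed, as a matter of a secondary outcome.

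**What to change.** 1. State that the intention-to-treat analysis of mean use includes all randomised patients, with 0 h/night for anyone who has not resumed, and remove the zero rule from the per-protocol clause.
2. Report mean use among resumers descriptively, without a test between arms.
3. Reconcile the adherence month: the analysis section counts from resumption and the outcomes section from the final consultation.
4. With 80% (intervention) to 94% (control) of values at zero on the plan's rates, base inference for the mean difference on robust standard errors or a permutation test stratified by centre, because normal residuals cannot be expected.
5. Limit the zero to patients without a device. A resumer whose recordings cannot be retrieved has missing data and belongs under the imputation rule.

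The cost is a few sentences of analysis text. No new data are needed, and neither the sample size nor the primary analysis changes.
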